### Randomisation and blinding

Randomisation for a 1:1 allocation of the study treatment is provided through an online-randomiser to ensure allocation concealment. This online-randomiser was integrated into the password-protected database. The randomisation took place immediately before the CS after having controlled the inclusion and exclusion criteria. The randomisation list was generated in Intercooled Stata Version 13.1 (StataCorp, College Station, TX, USA) using variable block sizes between 2 and 8. The list is safely stored in a separate and sealed file, which will only be opened if unblinding becomes necessary. This is considered to be unlikely since the concomitant treatment in case of insufficient uterine tone is independent of the mode of administration of carbetocin.

Subjects are randomised on arrival in the operating theatre to minimise the risk of dropouts after randomisation. To achieve similar numbers, randomisation is stratified for planned or unplanned CS (Fig. 1).

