#### Inclusion criteria

Healthy women with a singleton pregnancy undergoing a planned or unplanned CS after at least 37 completed weeks of gestation under regional anaesthesia (spinal, epidural or combined spinal-epidural anaesthesia) aged older than 18 years and with signed informed consent are eligible.

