### Study procedure

#### Standard care

After arrival of the patient in the operating theatre, the patient is positioned with a left uterine tilt to avoid aorto-caval compression. A fluid co-load of 500 ml hydroxyethyl starch HES 6 % is infused while the patient is monitored with pulse oximeter, electrocardiogram and non-invasive blood pressure cuff around the upper arm. Spinal anaesthesia by single-shot technique using hyperbaric bupivacaine 0.5 % 10 mg, fentanyl 10 mcg and morphine 100 mcg is applied in right lateral position. If an epidural catheter is already in place, 15–20 ml lidocaine 2 % with carbon dioxide and adrenaline 1:200,000 are administered through the catheter after an intrathecal or intravasal displacement has been excluded. After the application of the spinal anaesthesia, the patient is positioned in a left-tilted recumbent position. The CS is performed according to the in-house standard procedure applying the Misgav Ladach method for the laparotomy [14]. Following uterine incision, delivery of the baby and cord clamping, the placenta is delivered by cord traction or manually, if necessary.

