#### First secondary endpoint (or primary safety endpoint)

The haemodynamic parameters (lowest mean arterial pressure and highest heart rate within the first 5 minutes after administration of the study drug) are considered as primary safety endpoints.

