#### Statistical analysis plan

The following baseline characteristics will be used to investigate comparability of both trial arms: age, body mass index, parity, gravidity, gestational week, risk factors for PPH, number of previous CS, planned or unplanned CS, reason for CS, experience level of the obstetrician, batch number. Continuous variables will be described by using the mean (SD) or median (interquartile range) as appropriate, categorical variables by using count (percentage).

In order to answer the primary research question, a CI of the mean difference in LAS score of the maximal uterine tone within the first 5 minutes after cord clamping will be calculated. If the lower limit of this CI does not include the pre-specified non-inferiority limit of −10, an inferiority of a short-infusion of more than 10 points on the LAS as compared to a bolus application is unlikely. In order to improve efficiency, an additional model will be built adjusting for the most relevant confounders, such as experience of the obstetrician, parity or number of previous CS, number of risk factors for PPH (multiple pregnancy, abnormal placentation, history of PPH or uterine atony), duration of surgery, and duration of antenatal oxytocin infusion. In order to compare the change of the uterine tone over time between both study groups, a generalised estimation equation (GEE) [17] will be built using an exchangeable correlation matrix (with an interaction term between treatment group and time). Moreover, the uterine tone over time will be displayed graphically.

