The haemodynamic secondary outcomes (lowest mean arterial blood pressure and highest heart rate within the first 5 minutes after the administration of the study drug) will be analysed using a linear regression model adjusting for the corresponding baseline value and the amount of vasoactive drug administered during this period. In a further analysis, the course over time of mean arterial pressure and heart rate will be modelled using a GEE model with an exchangeable correlation matrix, using a knot at the average time of the lowest mean arterial pressure adjusted for the dosage of vasopressors administered, in order to compare the trend over time in both groups. Moreover, the change over time in blood pressure and heart rate will be displayed graphically. The incidence of any clinically relevant ST segment changes in both groups will be compared using a chi-squared or a Fisher’s exact test as appropriate. Further secondary endpoints will only be analysed descriptively. The comparison of the calculated blood loss will be adjusted in a linear regression model for whether or not the mother is breastfeeding.

All analyses and graphs will be performed using Intercooled Stata Version 13.1 for Mac (StataCorp, College Station, TX, USA). We will follow the Consolidated Standards of Reporting Trials (CONSORT) statement and its extension for non-inferiority trials for the future report [18, 19].

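### Anaesthesia type, a plausible predictor of lowest MAP and highest heart rate, is in neither the baseline list nor the haemodynamic models: a small, cheap gain in precision is forgone

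*Protocol article*

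**What the plan says.** - **Who is eligible.** Inclusion criteria: women "under regional anaesthesia (spinal, epidural or combined spinal-epidural anaesthesia".
- **What they receive.** Standard care describes "Spinal anaesthesia by single-shot technique using hyperbaric bupivacaine", with fentanyl and morphine and no adrenaline. Where a catheter is already in place, "15–20 ml lidocaine 2 % with carbon dioxide and adrenaline 1:200,000 are administered through the catheter".
- **Outcomes.** The primary safety endpoints are "lowest mean arterial pressure and highest heart rate within the first 5 minutes after administration of the study drug".
- **Model.** Statistical analysis plan: these outcomes "will be analysed using a linear regression model adjusting for the corresponding baseline value and the amount of vasoactive drug administered during this period". The only adjustment named for the haemodynamic GEE is vasopressor dose.
- **Baseline comparison.** The same section lists eleven characteristics, from age to "planned or unplanned CS, reason for CS, experience level of the obstetrician, batch number". None describes the anaesthetic.
- **Design.** Randomisation and blinding: 1:1 allocation on arrival in theatre, and "randomisation is stratified for planned or unplanned CS".
- **Power.** Haemodynamic measurement method: 80% power for at least 5 mmHg in MAP, type-1 error 5%, SD 10.

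**The concern.** The trial enrols women whose anaesthetics differ in route and drug content, and then measures blood pressure and heart rate in the minutes after the study drug. Whether a catheter is in place on arrival is known before randomisation and plausibly bears on both measurements. The article does not say that it does; this is an inference from the two regimens.

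Nothing named in the plan fully stands in for it:

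- The vasoactive drugs listed under Further secondary endpoints are phenylephrine, ephedrine, atropine and nitroglycerine. Epidural adrenaline is not among them, so the vasoactive-dose covariate as listed does not carry it. That covariate is also measured after randomisation.
- The baseline value may carry part of the technique effect, but the article does not say whether it is taken before or after the block, and it names no baseline term for the GEE.
- Planned or unplanned CS is related to catheter status but is not the same thing. Choice of study population justifies that stratum by earlier oxytocin exposure, and it is not a named term in the haemodynamic models.

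At stake are some precision in the endpoints meant to show the advantage of the short-infusion, and the chance to see whether the arms happen to differ in anaesthetic technique. For uterine tone, by contrast, the plan adds a covariate-adjusted model expressly to gain efficiency.

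**Working it through.** **Inputs from the article.** 63 per arm (Sample size justification); MAP difference 5 mmHg, SD 10, type-1 error 5%, taken as two-sided (Haemodynamic measurement method).

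**Assumptions, not in the article.** Share with an epidural p = 10–50%; difference in lowest MAP between techniques D = 3–10 mmHg.

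**Step 1: the plan's own figure.** Power = Φ(δ / (SD·√(2/n)) − 1.96).

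With n = 63, √(2/63) = 0.1782, so 5 / (10 × 0.1782) = 2.806 and Φ(2.806 − 1.96) = 80.1%. The stated 80% reproduces.

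**Step 2: gain from adjustment if SD 10 is the total SD.** Residual SD = √(100 − p(1−p)D²); power as in step 1 with that SD.

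| p | D (mmHg) | Residual SD | Power, 63 per arm |
|---|---|---|---|
| 10% | 3 | 9.96 | 80.4% |
| 20% | 5 | 9.80 | 81.7% |
| 50% | 5 | 9.68 | 82.6% |
| 30% | 8 | 9.30 | 85.5% |
| 50% | 10 | 8.66 | 90.0% |

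For D of 3–5 mmHg the gain over 80.1% is at most 82.6 − 80.1 = 2.5 points. All gains are upper limits, because the planned baseline term may already absorb part of the technique effect.

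**Step 3: chance imbalance without stratification.** 1.96 SD of the difference in epidural share between arms = 1.96·√(p(1−p)·2/63).

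- p = 10%: 10.5 percentage points. With D = 3, the MAP contrast shifts by 0.105 × 3 ≈ 0.3 mmHg.
- p = 50%: 17.5 percentage points. With D = 10, it shifts by 0.175 × 10 = 1.75 mmHg.

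**Step 4: effect of the stratification.** Replace p(1−p) by its average within strata. Assume half the sections are unplanned and 2% of planned cases have an epidural.

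- Epidural in 60% of unplanned cases: within-stratum variance 0.5 × 0.60 × 0.40 + 0.5 × 0.02 × 0.98 = 0.130. The 1.96-SD imbalance falls from 16.2 to 12.6 points.
- Epidural in 90% of unplanned cases: 0.5 × 0.90 × 0.10 + 0.5 × 0.02 × 0.98 = 0.055. It falls from 17.4 to 8.2 points.

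Stratification therefore limits the imbalance without removing it.

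**Heart rate.** The article gives no SD or target difference, so no corresponding calculation is possible.

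**The case against.** **Nothing here is an error.** A linear model with baseline value and vasoactive dose is coherent, and leaving out one more prognostic covariate does not invalidate it. A condensed article may also leave further covariates to a fuller plan that is not shown. This stands, and it is why the point is minor. Still, the article commits to explicit lists, detailed enough to include batch number, and a stated list can be improved.

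**A reader might infer that the stated power is too high.** If the SD of 10 held only within one technique, 30% epidural and a 10 mmHg difference would give SD √(100 + 0.3 × 0.7 × 100) = 11.0 and power of about 72%. The article does not support this. It does not call 10 a within-technique SD; read as the SD of the mixed population, it already contains that spread. The 72% also leaves out the planned baseline adjustment. With an assumed baseline–outcome correlation of 0.3 to 0.5, the residual SD is 11.0·√(1 − r²) = 10.5 to 9.5 and power is about 76% to 84%.

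**A reader might infer bias.** Under 1:1 randomisation, omitting a prognostic baseline covariate from a linear model costs precision; chance imbalance is already covered by the confidence interval and type-1 error. Stratification limits the imbalance, and two correlates, planned or unplanned CS and reason for CS, are in the baseline list. This stands. What remains is that an imbalance in technique itself would not be shown.

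**A reader might call technique a known determinant of these endpoints.** The article gives no such statement, no effect size and no interval between the epidural dose and the study drug. Plausible is as far as it goes.

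**Conclusion.** The point holds as a cheap improvement of minor severity. Anaesthesia type is absent from both the baseline list and the haemodynamic models, and it is a plausible predictor of both primary safety endpoints. The omission neither biases the comparison nor makes the 80% power wrong.

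The MAP gain runs from 0.3 to about 10 power points across the assumed range, and is under 3 points for technique differences of 3–5 mmHg, less what the baseline value absorbs. An undetected chance imbalance at the 1.96-SD level would shift the MAP contrast by about 0.3 to 1.75 mmHg before stratification and baseline adjustment reduce it. These sizes rest on assumed epidural shares and technique differences and on reading SD 10 as the total SD.

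**What to change.** Before unblinding, define one binary variable: epidural catheter in place on arrival in theatre, yes or no. Class it by what is known before randomisation, whatever technique is finally used. A woman whose catheter fails and who then receives a spinal stays a yes, so the variable remains a true baseline factor.

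1. Add it to the baseline characteristics in the Statistical analysis plan section.
2. Pre-specify it as a covariate in the linear models for lowest MAP and highest heart rate.
3. Pre-specify it in the haemodynamic GEE.

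The cost is one degree of freedom per model, one row in the baseline table and one item taken from the anaesthesia record. No trial procedure changes. The article describes a trial still enrolling with a blinded statistician, so the covariate can be fixed credibly if this is done and dated before the allocation is opened.

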#### Concomitant treatments

In case of insufficient uterine tone, the patient will be treated according to the current standard of care. There are six options: (1) uterine massage, (2) sulprostone 4–8 mcg/min, (3) 600 mcg misoprostol rectal, (4) oxytocin infusion 20–40 U/2 h, (5) Bakri™ balloon, and (6) surgical (including Tachosil®) or radiological (embolisation) intervention. The choice of one or several of these interventions is according to the severity of uterine atony and at the discretion of the treating obstetrician.

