#### Laboratory analyses

Haemoglobin and haematocrit levels are measured preoperatively and 2 days postoperatively in order to estimate the perioperative blood loss taking into account the calculated pregnancy blood volume and the percent blood volume lost [15, 16].

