### Choice of primary endpoint

We consider the choice of the appropriate measurement of our primary endpoint as a main challenge in this trial. The choice of our primary outcome is based on a randomised controlled trial performed by Butwick et al. [11] who also used a LAS ranging from 0 to 10 to assess uterine tone in a similar setting. We expanded the scale from 0 to 100 to avoid the fact that some outcome assessors used decimal places (e.g. 7.5) while others did not. Moreover, manual palpation of the uterus represents the standard method to assess uterine tone in daily clinical practice. To reduce bias, especially when using a subjective primary outcome measurement, we have established and will maintain blinding by using a double-dummy technique for study drug administration in patients and all care providers until the statistical analysis has been performed. We have chosen to abstain from a binary assessment of the uterine tone as it would be too parallel to our secondary outcome variable ‘any additional uterotonics – yes/no’. The objective efficacy outcome of interest would have been intraoperative blood loss. Blood loss during PPH is often estimated visually, but visual assessment has been shown to be imprecise, usually underestimating blood loss particularly concerning larger volumes [21–24]. We have, therefore, decided to choose the uterine tone as our primary outcome variable. We consider blood loss as a secondary endpoint, calculated by taking into account the pre- and postoperative haematocrit and the estimated blood volume of the parturient [15].

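### Calculated blood loss is to be compared after adjusting for breastfeeding, a variable that arises after randomisation and treatment; this can distort the randomised comparison, and no reason is given

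*Protocol article*

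**What the plan says.** Under Statistical analysis plan, the article fixes the blood-loss analysis in one sentence: "The comparison of the calculated blood loss will be adjusted in a linear regression model for whether or not the mother is breastfeeding". Breastfeeding is the only covariate named. No reason is given, and no unadjusted comparison is named as the main one. The sentence just before it reads "Further secondary endpoints will only be analysed descriptively", and blood loss over 48 hours is listed under Further secondary endpoints.

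The timing is clear from other sections. Under Randomisation and blinding: "The randomisation took place immediately before the CS after having controlled the inclusion and exclusion criteria". The study drug follows cord clamping (Study treatment in intervention and control group). Under Laboratory analyses: "Haemoglobin and haematocrit levels are measured preoperatively and 2 days postoperatively in order to estimate the perioperative blood loss". Breastfeeding is not in the list of baseline characteristics.

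On the standing of the endpoint, Choice of primary endpoint says "The objective efficacy outcome of interest would have been intraoperative blood loss", and then "We consider blood loss as a secondary endpoint, calculated by taking into account the pre- and postoperative haematocrit".

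**The concern.** A randomised comparison is protected because nothing measured before allocation can differ between arms except by chance. A covariate that arises after treatment does not have that protection. Whether a mother breastfeeds is settled after the study drug has been given and while the blood loss being measured is still accruing. It may therefore be partly a result of that loss, or be affected by treatment in some other way. Holding it fixed can remove part of a real difference or create one that is not there.

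The primary endpoint is uterine tone judged by palpation, which the article itself treats as subjective. Calculated blood loss is the most objective efficacy outcome beside it, and the section on the choice of a non-inferiority design names elevated blood loss as the underlying risk. If the short-infusion cost some extra blood, an estimate shrunk towards zero would make that cost look smaller, next to a claim that the short-infusion is no worse.

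**Working it through.** **The plan's own figures.** The article gives no figure for the blood-loss comparison. Its only related design figure is the primary sample size, which reproduces: n per group = 2 × (1.960 + 0.842)² × 20² / 10² = 62.8, so 63; then 126 / 0.9 = 140. The covariate has no bearing on these numbers.

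**Order of events.** Preoperative haematocrit and planned/unplanned status come before the study drug. The sequence is then randomisation, caesarean, cord clamping, study drug, blood loss and start of breastfeeding, and the day-2 haematocrit. Breastfeeding is thus post-randomisation and inside the outcome window.

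**What adjustment does.** Let T be treatment (1 = short-infusion), Y blood loss in SD units and B breastfeeding (0/1). In least squares,

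adjusted difference = unadjusted difference − b × (breastfeeding rate in T=1 − rate in T=0),

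where b is the within-arm slope of Y on B. The two differences part only if the breastfeeding rates differ between arms and breastfeeding is associated with loss within arms. If B depends on treatment only through Y, with within-arm correlation r, the subtracted term is about r² times the true difference, so the adjusted difference is about (1 − r²) times the truth.

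**Simulation.** All inputs are assumed, because the article gives no blood-loss SD, breastfeeding rate or link between the two. Y = τT + standard normal noise; logit P(B=1) = a + ln(OR) × Y + h × T; 2 million records per scenario, so the results show expected values rather than sampling noise.

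*Loss affects breastfeeding (h = 0).* Each cell shows unadjusted → adjusted difference in SD, with the shrinkage computed before rounding.

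| OR of breastfeeding per SD more loss | τ=0.25, control rate 82–88% | τ=0.5, control rate 82–88% | τ=0.25, control rate 65–70% | τ=0.5, control rate 65–70% |
|---|---|---|---|---|
| 1 | 0.248 → 0.248 (0%) | 0.501 → 0.501 (0%) | 0.248 → 0.248 (0%) | 0.500 → 0.500 (0%) |
| 0.75 | 0.249 → 0.247 (0.9%) | 0.500 → 0.495 (0.9%) | 0.252 → 0.248 (1.7%) | 0.501 → 0.492 (1.7%) |
| 0.5 | 0.250 → 0.237 (5.3%) | 0.500 → 0.472 (5.6%) | 0.249 → 0.226 (9.2%) | 0.500 → 0.455 (9.1%) |
| 0.25 | 0.249 → 0.202 (18.7%) | 0.499 → 0.399 (20.1%) | 0.249 → 0.188 (24.6%) | 0.497 → 0.373 (25.0%) |

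With τ = 0 and h = 0, the adjusted difference is zero, apart from simulation noise, at every odds ratio.

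*Treatment lowers breastfeeding by another route, no true difference in loss (τ = 0).* With h = −0.5 the adjusted difference is −0.02 SD at OR 0.75 and −0.04 SD at OR 0.5. With h = −1 it is −0.04 and −0.10 SD. The last case agrees with the identity: the rates are 0.711 and 0.863, a gap of −0.152; with b of about −0.64, 0 − (−0.64 × −0.152) = −0.097. Under these assumed signs, the spurious difference favours the short-infusion.

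*Breastfeeding affects loss, treatment does not affect breastfeeding.* With an effect of −0.3 SD, both estimates are 0.249, so there is no bias.

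**Ceiling on the shrinkage.** B is binary. For normally distributed Y, the largest possible correlation is φ(z_p)/√(p(1−p)), reached only if loss alone decided who breastfeeds. At p = 0.90 this is 0.1755/0.300 = 0.585, so r² is at most 0.34. At p = 0.95 it is 0.1031/0.218 = 0.473, so r² is at most 0.22. A shrinkage of 25% needs r = 0.5, which is near the ceiling at 90% and beyond it at 95%.

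**The case against.** The strongest reply is that the article shows no bias. It nowhere says that blood loss affects breastfeeding, and it gives no rate. If breastfeeding instead influences blood loss and treatment leaves breastfeeding alone, the adjustment does no harm. The endpoint is secondary: non-inferiority is decided on uterine tone in both the intention-to-treat and the per-protocol analysis. The endpoint is defined as a mean, so the group means would probably be reported as well. All of this stands, and it limits the point to a distortion that is possible, not demonstrated. It does not supply a reason for the covariate, and the article does not make the unadjusted contrast the main one.

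A reader might infer several stronger points that the document does not support:

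- **That the adjustment always pulls towards no difference.** This holds only where loss drives breastfeeding; the other route can create a difference.
- **That a quarter of the effect would be lost.** That needs a link near or beyond what a binary covariate allows when most mothers breastfeed.
- **That blood loss is the only objective efficacy comparison.** Additional uterotonics and blood products or coagulation factors are also listed. Treatment of low tone is, however, chosen "according to the severity of uterine atony and at the discretion of the treating obstetrician", so additional uterotonics depend on judgement. The sentence on the objective outcome of interest also concerns intraoperative loss, not the calculated 48-hour loss.
- **That the plan contradicts itself by setting a regression after "Further secondary endpoints will only be analysed descriptively".** The regression sentence follows directly and reads as an unmarked exception.
- **That leaving out the stratum and preoperative haematocrit is an error.** In a secondary model this is a choice about precision.

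**Conclusion.** The point holds as a minor one. The plan conditions its blood-loss comparison on a variable that arises after randomisation and treatment, without a stated reason, and this can distort the randomised contrast. Under assumed links, a true difference shrinks by 1 to 2% (odds ratio 0.75 per SD), 5 to 9% (0.5) or 19 to 25% (0.25, a very strong link). A spurious difference of 0.02 to 0.10 SD can appear if treatment also affects breastfeeding by another route. Bias is nil if treatment changes neither loss nor breastfeeding, or if breastfeeding and loss are unrelated within arms. The document does not allow a choice between these cases. The sample size and the non-inferiority decision are unaffected. What is at stake is the soundness of the most objective check on a subjective primary endpoint, where shrinkage would be falsely reassuring.

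**What to change.** Make the main blood-loss comparison a linear regression of calculated blood loss on treatment, adjusted only for the planned/unplanned stratum and preoperative haematocrit, and report the difference with its 95% CI. Both covariates are fixed before the study drug is given and are already collected. Drop the breastfeeding-adjusted model, or keep it as a labelled exploratory analysis with its reason stated. Say in the text that blood loss is an exception to the descriptive-only rule.

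The cost is a change of analysis wording, made before unblinding: no new data and no extra patients. Replacing breastfeeding with an intention to breastfeed stated before surgery is not equally cheap. The article does not say that this is recorded, and 60% of patients had been enrolled when it was submitted.

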### Statistics

#### Sample size justification

To be 80 % sure that the lower limit of a one-sided 97.5 % confidence interval (CI) will be above the non-inferiority limit of −10 points on the LAS, 63 patients per group are required assuming a standard deviation (SD) of 20. Offsetting a maximal dropout of 10 %, this leads to a total sample size of 140 patients. The non-inferiority margin has been defined to be −10 on the LAS by the four most senior obstetricians at our institution. The SD had been derived from the results of a trial by Butwick et al., who used the same scale to assess the uterine tone [11].

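### The regression for calculated blood loss names breastfeeding as its only covariate and leaves out preoperative haematocrit and blood volume, giving up a modest amount of precision at no saving

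*Protocol article*

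**What the plan says.** The section on laboratory analyses states the purpose of the blood samples: "Haemoglobin and haematocrit levels are measured preoperatively and 2 days postoperatively in order to estimate the perioperative blood loss". The section on further secondary endpoints defines the outcome as calculated maternal blood volume times the percentage of blood volume lost, over 48 hours. The discussion of the primary endpoint confirms the ingredients: blood loss is "calculated by taking into account the pre- and postoperative haematocrit and the estimated blood volume of the parturient".

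The statistical analysis plan section then fixes the model: "The comparison of the calculated blood loss will be adjusted in a linear regression model for whether or not the mother is breastfeeding". No other covariate is named, and preoperative haematocrit is not in that section's list of baseline characteristics either. The lowest mean arterial pressure and highest heart rate are treated differently. They "will be analysed using a linear regression model adjusting for the corresponding baseline value and the amount of vasoactive drug administered during this period".

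Two statements bear on how much weight the comparison carries. Just before the blood-loss sentence the article says: "Further secondary endpoints will only be analysed descriptively". The discussion of the primary endpoint says: "The objective efficacy outcome of interest would have been intraoperative blood loss".

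**The concern.** Calculated blood loss is a relative fall from a measured baseline, scaled by a quantity known before treatment. Part of its spread between women therefore comes from the preoperative haematocrit (including its measurement error) and from blood volume. A regression that includes both removes that part from the residual. The stated model leaves it in, although the article already uses baseline adjustment for the haemodynamic outcomes and adds covariates to the primary analysis to gain efficiency.

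What is at stake is the width of one secondary confidence interval. That interval has some importance because the primary endpoint is a palpation score, and calculated blood loss is the only objective efficacy outcome for which the article states a model. A needlessly wide interval makes it a little harder to exclude greater blood loss with the slower administration.

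**Working it through.** **The plan's own figure.** The only sample size is for uterine tone: "To be 80 % sure that the lower limit of a one-sided 97.5 % confidence interval (CI) will be above the non-inferiority limit of −10", with SD 20. n per arm = 2 × (1.960 + 0.842)² × 20² / 10² = 62.8, so 63; 126 / 0.90 = 140. Both reproduce. No SD, effect or power is given for blood loss, so everything below rests on assumed inputs, with 63 analysed per arm.

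**Form of the outcome.** The article does not print the formula. I take L = V × (H0 − H2) / H0, with V blood volume, H0 preoperative and H2 day-2 haematocrit, and V computed from data on hand before surgery.

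**Direction of the haematocrit slope.** Let b = correlation × SD(H2) / SD(H0). To first order the slope of L on H0 is V × (mean H2 / mean H0² − b / mean H0). Assume means 36 and 32, SD(H0) 3 and V 6000 ml:

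- correlation 0.4, SD(H2) 3.0: b = 0.40, slope = 6000 × (0.0247 − 0.0111) = about +81 ml per point (simulated +83);
- correlation 0.5, SD(H2) 3.0: b = 0.50, slope = 6000 × (0.0247 − 0.0139) = about +65 (simulated +66);
- correlation 0.8, SD(H2) 4.0: b = 1.07, slope = 6000 × (0.0247 − 0.0296) = about −30 (simulated −30).

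The slope changes sign at b = 32/36 = 0.89, so a high preoperative value does not always go with a higher calculated loss.

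**Precision.** Adjusted SE / unadjusted SE = √(1 − R²), with R² from regressing L on H0 and V. First set of assumptions (SD of V 700 ml, 400,000 draws each):

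| Correlation | SD(H2) | R² | SE reduction |
|---|---|---|---|
| 0.5 | 3.0 | 0.19 | 1 − √0.81 = 10.0% |
| 0.5 | 3.5 | 0.10 | 1 − √0.90 = 5.1% |
| 0.6 | 3.0 | 0.14 | 1 − √0.86 = 7.3% |
| 0.6 | 3.5 | 0.06 | 1 − √0.94 = 3.0% |

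Over correlation 0.4 to 0.8 and SD(H2) 3 to 4, R² runs from about 0.03 to 0.24, an SE reduction of about 1 to 13%.

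The second set works from a true fraction lost plus noise: haematocrit SD 3, noise SD 0.5 to 2 points, fraction lost mean 0.12 and SD 0.04 to 0.08, SD of V 700 to 900 ml. R² is 0.03 to 0.14, an SE reduction of 1 − √0.97 = 1.5% to 1 − √0.86 = 7.3%. Blood volume contributes even when haematocrit noise is small, because it multiplies the outcome. Preoperative haematocrit alone, with its SD also varied from 2.5 to 3.5, has a correlation of 0.03 to 0.45 with the loss, an SE reduction of about 0 to 11%.

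These are large-sample figures. Estimating two extra coefficients from 126 women multiplies the variance by about 123/121 = 1.017, or the SE by 1.008, so the smallest gains nearly vanish.

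As a yardstick, an SE reduction of 2 to 7% multiplies the effective sample size by 1/0.98² = 1.04 to 1/0.93² = 1.16, equivalent to about 5 to 20 more women on 126.

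**Validity.** In 4,000 simulated trials per setting (haematocrit SD 3, fraction-lost SD 0.06), type I error without and with preoperative haematocrit was 5.1% and 5.1% (noise 1 point), and 5.1% and 5.2% (noise 1.5 points). Both estimators were unbiased. Power for an assumed 200 ml difference was 70.5% and 70.8%, and 57.9% and 59.3%.

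**The case against.** The strongest reply is that nothing here is invalid. Randomisation protects the comparison with or without the baselines, and the simulations bear this out. That stands in full.

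A reader might infer that a chance difference in preoperative haematocrit would show up as a false treatment effect. The documents do not support that. Chance imbalance is part of the sampling variation that the unadjusted interval already covers. With SD 3, one standard error of the baseline difference is 3 × √(2/63) = 0.53 points. At 33 to 66 ml per point this moves the estimate by about 17 to 35 ml, against a standard error of about 78 to 97 ml (SD of loss 440 to 545 ml × √(2/63)). The slope itself may also be near zero or negative.

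A reader might also take this for the trial's only objective efficacy comparison. It is not: additional uterotonics and blood products are also reported, though only descriptively, and uterotonic use is at the obstetrician's discretion. The article's remark about the objective outcome of interest concerns intraoperative loss, not the 48-hour calculated loss. Blood loss is a further secondary endpoint and plays no part in the non-inferiority conclusion.

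Finally, a journal article condenses, and a fuller covariate list may exist elsewhere. This limits the point to the model as written. It does not remove it, because the article does state a model with a named covariate and names baselines for its neighbours.

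**Conclusion.** The point holds as a minor matter of efficiency. The stated regression omits two pre-treatment components of its own outcome, out of line with the baseline adjustment used for the haemodynamic outcomes. The cost is precision only: about 1 to 13% of the standard error over the ranges tried, typically 2 to 7%, slightly less after allowing for the two extra coefficients. There is no bias and no inflation of type I error.

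The omission is plain in the text. The size is not: every haematocrit and volume input is assumed, as is the formula for the percentage lost, and the direction of the haematocrit effect cannot be settled from the article.

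**What to change.** Before unblinding, prespecify a linear regression of calculated blood loss on treatment arm, preoperative haematocrit and calculated maternal blood volume, and report the adjusted difference with its 95% confidence interval. Add preoperative haematocrit to the table of baseline characteristics. Whether breastfeeding should stay in the model is a separate question that this change does not depend on.

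The cost is one line of analysis wording and two degrees of freedom. No new data are needed and the sample size of 140 is unaffected. The article reports 60% enrolment at submission and a statistician blinded until the data are analysed, so the change could still be prespecified at that stage.
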